#### ***Initial Assessment of Exercise Tolerance***

All enrolled patients will complete the remainder of the PROMIS Physical Function 12a Short Form and participate in two physical screening tests to determine participation in the exercise and nutrition interventions and to evaluate exercise tolerance.

- PROMIS questions PF6, PFC29, PFA55, PFC53, PFA9 and PF\_23 must be answered with a 5, 4 or 3 to participate in the exercise and nutrition interventions.
- Any answer of 1 or 2 on the PROMIS will result in the patient being excluded from participation.
- Patients must be able to perform the following tests to participate in the exercise and nutrition intervention. Patients who cannot perform both tests will be excluded from participation.
  - 5x sit-to-stand
  - 6 minute walk test (6MWT)

#### ***Exercise Intervention***

The American College of Sports Medicine exercise guidelines for cancer survivors encourage a combination of 150 minutes of moderate-intensity aerobic activity and two

to three weekly sessions of strength training but caution that exercise programs should be adapted to the needs of each cancer survivor [7]. These exercises may be completed as part of a home-based rehabilitation and exercise program. For example, a home-based exercise program incorporating a walking and gentle strengthening program was tolerable and had positive effects on fatigue and physical function in stage IV lung and colorectal cancer patients [8]. The Rapid, Easy, Strength Training exercise protocol used in this study at the Mayo Clinic targeted multiple major muscles groups in the upper and lower limbs [8].

The home-based exercise program in this current study will incorporate both aerobic and strengthening program components at a less rigorous level than the exercise guidelines recommended by the American College of Sports Medicine, in order to ensure safety and encourage adherence. ***The exercise regimen will include A) a graded resistance/strengthening program and B) a walking program conducted during the preoperative treatment period.***

- An MDACC physical medicine and rehabilitation (PM&R) physician will supervise the conduct of the exercise intervention.
- A Kinesiology PhD candidate with an American College of Sports Medicine Personal Trainer certification and a research staff member will implement the exercise intervention, including demonstration of strengthening exercises upon verification of participation.
- All exercises will be clearly described in an exercise demonstration video (produced specifically for this program) and within the study booklet provided to all patients (attached). In addition, the exercises will be described and demonstrated in-person by the study staff. The demonstration video, photographs and descriptions of exercises in the study booklet, and in-person demonstrations will all include proper instructions for setting up resistance tubes and safety tips for each exercise. The study booklet will also include exercise logs in which the patients should record their daily exercise activity. Participants will choose to record daily exercise using these paper logs or using a secure MD Anderson electronic system.
- The preoperative period varies in terms of both the types of treatments that patients undergo and the length of therapy. Approximately 70% of patients with technically resectable tumors undergo chemotherapy (6-12 weeks) followed by chemoradiation (2-6 weeks) and then a recovery period (4-6 weeks) before surgery. Approximately 20% of patients undergo chemoradiation (2-6 weeks) and then a recovery period (4-6 weeks) before surgery. Approximately 10% of patients undergo chemotherapy (6-12 weeks) and then a recovery period (4-6 weeks) before surgery. The exercise intervention will be performed throughout the treatment course.

#### **A. Resistance/strengthening**

**All participants will be instructed to perform resistance/strengthening exercises for a 30-minute period at least twice a week.** The goal is to achieve moderate

exercise intensity (12-13 on the Borg Rating of Perceived Exertion (RPE) scale, included in patients' study booklets). The strengthening exercises used in this study are designed to engage proximal upper body muscles, shoulder muscles, abdominal muscles, back extensor muscles, and hip and leg muscles. Strengthening these muscle groups will develop the participant's trunk control and balance, which we believe will help with mobility during the prehabilitation phase and in the post-operative period. Furthermore, maintaining and developing the shoulder, back and leg muscles are important for transitional activities such as transferring into and out of bed, which is important after an extensive abdominal surgery such as a pancreatectomy.

**Participants will be instructed to perform any 8 strengthening exercises for a total duration of 30 minutes.** Each patient will be issued a set of 3 resistance exercise tubes with which the exercises can be performed. The strengthening exercises consist of seated and standing weight-bearing exercises. A variety of exercises targeting different muscle groups will be prescribed to minimize plateauing, and to generate increased interest and motivation (and thus, adherence). Participants will perform 3 sets of 8-12 repetitions each of each exercise. Once they are able to perform 3 sets of 12 repetitions of an exercise, they will graduate to the next level of increasing resistance as denoted by the color of the resistance tube used.

Prior to initiating the strengthening exercises, each participant will initiate a series of 5 *standing warm-up exercises* before each resistance exercise session that will help with balance.

Participants will select the 8 exercises to be performed from 19 strengthening exercises that include:

- *Upper body strengthening exercises* consist of seated and standing exercises to strengthen the deltoids, triceps, biceps, and rotator cuff. These exercises will include (but are not limited to) bench press, chest press, and biceps curls using resistance tubes.
- *Abdominal strengthening exercises* that will be performed while seated or standing using resistance tubes, which will be more tolerable as older adults may not be able to tolerate the supine-position abdominal exercises.
- *Lower body strengthening exercises* that consist of *seated and standing* exercises to strengthen the gluteus musculature, quadriceps, hamstrings, and gastrocnemius-soleus complex. These exercises will include (but are not limited to) leg lifts, leg extensions, hip extensions, and hip abductions. Most exercises will be performed using resistance tubes.

Participants will record the date, resistance (color of resistance tube used), number of repetitions in each set, and their perceived intensity of a resistance exercise session based on the Borg Rating of Perceived Exertion (RPE) scale (the scale will be included in the participants' exercise program packets). They will also record the total time spent on their strengthening program after each exercise session. When each patient completes the exercise portion of the study, they will be asked which exercises they preferred.

The participants will be *encouraged* to complete an additional 5 minutes of stretching before and after resistance exercise sessions. Instructions and photographs of stretches targeting muscles in the upper body, back, and legs are included in the exercise program packets.

### **B. Walking program**

**The walking program will consist of walking briskly for a duration of 20 - 30 minutes per day, with a frequency of at least 3 times per week.** The goal is to achieve a moderate intensity of exercise (Borg RPE of 12 - 13). If the participant is unable to tolerate walking briskly, they will be instructed to walk at a tolerable pace for 20 to 30 minutes during each walking session. Each participant will be provided a pedometer and will be instructed to record the number of steps taken each day in addition to the total time spent during each walking session.

The participants will be provided with exercise logs (both electronic, using MD Anderson's Research Electronic Data Capture - REDCap – system, and paper forms) in which they will record their daily physical activity. Participants will choose whether to record daily physical activity and exercise activities using REDCap or paper logs.

### ***Emergency contacts***

The booklet provided to all patients will include emergency 24/7 contacts (physician, co-PI) in the event of an acute musculoskeletal injury or cardiopulmonary distress. In the event that this occurs, the patient will be managed with an appropriate medical referral. If the patient develops a musculoskeletal injury, they will be triaged to speak with one of the PM&R research team members. Patients who develop disease progression and/or have significant cancer treatment-associated toxicity will also be counseled on the continuation of this exercise program accordingly.

### ***Adherence/compliance***

To monitor for adherence and screen for any exercise intolerance or exercise barriers, all participants will be contacted by the research staff via telephone every two weeks. The research staff will be provided with a list of screening questions (attached) to address exercise adherence and assess for the need to advance the strengthening program. The research staff will also implement behavior interventions to encourage continued adherence to the exercise program that will include education on the benefits of exercise and physical activity.

It is anticipated that a fully adherent participant would be able to complete at least 60 minutes of moderate-intensity walking and 60 minutes of moderate-intensity resistance exercise per week. Adherence to the program will be based on completion of a variety of strengthening exercises (eight or more per session) and the total time spent performing both the walking and strengthening components. A participant who is able to complete 60 minutes of walking and 60 minutes of resistance exercise per week during each phase of neoadjuvant therapy will be classified as 100% adherent during that phase.

### ***Distress Plan***

In the event that a patient has difficulty with any study-related questionnaires or where the patient requests assistance for distress or where a practitioner determines that there is cause for concern, patients will be referred for assessment to a certified professional for assistance in managing their distress.

#### ***Equipment provided***

- Notebook for the exercise activity logs and written/photo exercise guides
- Pedometer: \$20 Omron HJ-321 TriAxis pedometer:  
<http://www.amazon.com/Omron-HJ-321-Tri-Axis-Pedometer-Black/dp/B007ZWIJR2>
- Resistance exercise tube set (set of 5, patients will be provided with the 3 with lowest resistance) including door anchor, ankle strap, and handles, \$32.99 per set)

#### ***Nutrition intervention***

Within 7 days of enrollment, a registered dietitian (RD, ie the study dietitian or delegate RD) will conduct a complete nutritional assessment. Each subject will be then be provided with individualized recommendations for calorie, protein, and fluid intake, tools for tracking intake (ie, diet log), as well as goals for weight maintenance, weight gain, or weight loss depending on stage of treatment/recovery. Patients will also be instructed to eat a high protein snack/meal/shake (~20 g) within one hour after strengthening exercises.

As is current “standard of care” for our patients who undergo pancreatic surgery, all patients will also receive instruction on the use of an immune enhancing oral supplement (Impact Advanced Recovery) for 5 days preoperatively (preop days 6 through 1).

When the research staff contacts the participants via telephone to monitor their exercise program, they will also be asked questions regarding their compliance with the nutritional plan. The research staff will be provided with a list of questions to assess patient understanding of and ability to comply with nutrition recommendations. If patients are non-compliant or have difficulty comprehending the nutritional program, the RD will be notified and RD will follow up with the patient for reeducation or adjustment of goals. To monitor compliance with immune enhancing oral supplement, the patient/family will be interviewed following surgery to determine consumption.

## **VII. Statistics**

This is a pilot study to assess the feasibility of a provider-supervised prehabilitation program among pancreatic patients who are undergoing neoadjuvant therapy. The prehabilitation program will include both exercise and nutrition interventions, where the exercise intervention will incorporate resistance/strengthening and walking programs. Adherence will be defined as the ability of each patient to complete  $\geq 60\%$  of the planned exercise intervention based on the total time spent performing the exercises relative to the total duration of therapy or total duration of recovery for a given phase. The primary endpoint, feasibility, will be established if  $\geq 60\%$  of the patients are adherent during a phase of therapy. That is, the prehabilitation program is deemed as feasible during a specific phase of therapy if 60% or more of the participants complete at least 60% of the weekly prescriptions for 60 minutes of walking and 60 minutes of strengthening

exercises during that phase of therapy. The calculation will account for the potential difference in the length of therapy among patients. The target weekly total exercise hour will be 120 minutes (including 60 minutes of walking and 60 minutes of strengthening exercises), thus we can derive the total prescribed hour for a given patient in a given phase considering his/her total treatment or recovery duration for that phase. Then, based on the recorded total hours of exercise intervention for that patient, we can calculate the % of completion for that patient in a given phase. If the % is at least 60% for a phase, we would define that patient as “adherent” for that phase. For the primary analysis, we will analyze the % adherence by phase, where “phase” could be chemotherapy phase, chemoradiation phase or recovery phase. As a secondary analysis, we will further differentiate whether patients receive chemoradiation from start or chemoradiation is given following chemotherapy and analyze these two subgroups of patients separately. Similarly, we will differentiate patients in recovery phase based on the therapies they receive prior to the recovery (i.e., chemotherapy only, chemoradiation only or chemotherapy plus chemoradiation).

The study was originally designed to enroll 50 patients and as of August 2015, 20 patients have been enrolled under this initial design. We have placed the study on hold until these attached revisions are made because we have encountered several issues with the first design and have identified solutions to these problems. The primary issue is that, under the old design, we would assess the exercise intervention in a 6-week period regardless of the treatment phase. Initial analysis of the data has shown us that patients’ adherence depends to a large degree on the phase of therapy. For example, patients seem to be less compliant with exercise during chemotherapy than they are during either chemoradiation or rest. Future trials will require us to time the intervention precisely and optimize the intervention during preoperative therapy, so we need to know the best “phase” (or phases) of therapy to deliver the exercise intervention. This trial will allow us to gain a more accurate and better understanding about patients’ adherence during each phase so as to guide the focus for future studies.

We have also changed a couple of the survey tools and assessments we will use in this new design, as described below. We added tools to help us explore barriers to exercise and we improved a physical assessment from one with low resolution to one with higher resolution (and, it is used more frequently in the literature).

Under the revised design, we will enroll 50 new patients and evaluate the feasibility of the exercise intervention through assessing their adherence rate during each phase of the neoadjuvant therapy. We assume that among the 50 patients, 35 patients will receive chemo followed by chemoradiation, recovery and then surgery; 10 patients will receive chemoradiation followed by recovery phase and then surgery; and 5 patients will receive chemotherapy followed by recovery phase and then surgery. Therefore, overall we will have 40 patients’ data for assessing the adherent rate in the chemotherapy phase, 45 patients’ data for assessing the adherent rate in the chemotheradiation phase and 50 patients’ data for the recovery phase. Thus, with a sample size of 40, 45 and 50 and assuming an adherence rate of 60%, the exact 95% confidence interval will be (43%, 75%), (44%, 74%) and (45%, 74%), respectively.

Descriptive statistics, such as frequency (percentage) and median (range) will be used to summarize the data, including patient demographics, clinical features, comorbidity,

symptoms burden and quality of life. We will also summarize patients' tolerance for specific exercises, their ability to advance the exercises and the motivating/prohibiting factors for them to complete the study materials. The rate of adherence will be estimated for each phase, along with the exact 95% confidence interval. Similarly, the proportion of patients with frailty (i.e., abnormality in 3 or more of 5 markers), perioperative complications (yes/no; high/low grade) and physical/functional measures (yes/no for completing the 5x sit-to-stand test and the 6-minute walk test) will be estimated, along with the exact 95% confidence intervals. As an exploratory analysis, we will fit a multiple logistic regression model to assess the association between patient characteristics and socioecological characteristics (social support for exercise and neighborhood walkability) and adherence (yes/no) for each phase. In addition, paired t-test or Wilcoxon signed rank test will be used to assess the change of Fact-Hep, Frailty, physical functioning, and exercise capacity measures from baseline. We will also fit a linear mixed model to assess the change of each measurement over time (i.e., at enrollment, pre-op and post-op visit), while accounting for the correlation among multiple observations from the same patient.

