## **IV. INCLUSION CRITERIA**

- 1) Pancreatic adenocarcinoma, biopsy-proven or suspected
- 2) Scheduled for intended pancreatectomy, > = 6 weeks until planned resection
- 3) Scheduled for neoadjuvant chemotherapy and/or chemoradiation for pancreatic cancer
- 4) Able to understand the description of the study and willing to participate.
- 5) Able to understand the exercise intervention and able to maintain a daily exercise log.
- 6) Participant must have telephone access and agree to engage with telephone access with the research personnel.

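### The adherence denominator covers the whole treatment phase, but nothing requires exercise to start before the phase does, so a late starter faces a stricter cut-off

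*Protocol*

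**What the plan says.** All references are to the prehabilitation protocol (2014-0702).

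- **Denominator.** VII. Statistics scores each patient and phase "based on the total time spent performing the exercises relative to the total duration of therapy or total duration of recovery for a given phase". It then gives the formula: a weekly target of 120 minutes, applied to the "total prescribed hour for a given patient in a given phase considering his/her total treatment or recovery duration for that phase". The one stated adjustment is for patients whose therapy differs in length.
- **Cut-offs.** A patient is adherent in a phase at 60% or more of the prescribed time. The programme is feasible in that phase if "60% or more of the participants complete at least 60% of the weekly prescriptions".
- **Entry.** The only time limit in IV. Inclusion Criteria is "Scheduled for intended pancreatectomy, > = 6 weeks until planned resection". A separate criterion asks that the patient be scheduled for chemotherapy, chemoradiation or both. Neither says that therapy must not have begun.
- **Phase lengths.** Under Exercise Intervention, about 70% of patients "undergo chemotherapy (6-12 weeks) followed by chemoradiation (2-6 weeks) and then a recovery period (4-6 weeks) before surgery". About 20% have chemoradiation then recovery, and about 10% chemotherapy then recovery.
- **Planned counts.** VII. Statistics counts 40, 45 and 50 patients in the chemotherapy, chemoradiation and recovery phases.

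**The concern.** Weeks of a phase that pass before a patient has been taught the exercises enter the denominator but cannot produce logged minutes. The score therefore mixes two things: how well a patient followed the programme, and how late the patient began it.

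The error has one direction. It can only lower the score, and only in the phase the patient joins. On the most common pathway that is chemotherapy, or chemoradiation if entry is later. VII. Statistics says the redesign is meant to show which phase or phases suit the intervention best. A late start in one phase could then be read as poor feasibility in that phase.

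**Working it through.** **Inputs.** Weekly target 120 minutes, patient cut-off 60%, phase cut-off 60%, and n = 40, 45, 50 (VII. Statistics). Chemotherapy 6–12 weeks, chemoradiation 2–6, recovery 4–6 (Exercise Intervention). Entry at least 6 weeks before planned resection (IV. Inclusion Criteria). The share of patients who start part-way through a phase is not in the protocol; I assume 0–30%.

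**The plan's own figures.** Exact (Clopper-Pearson) 95% intervals at 60% are 24/40: 43.3–75.1%; 27/45: 44.3–74.3%; 30/50: 45.2–73.6%. These agree with the protocol. The point concerns what is counted, not these intervals.

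**Score of a late starter.** Let L be the phase length in weeks, e the weeks elapsed when exercise starts, f = e/L, and a the share of the weekly target achieved afterwards.

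- Score = 120·a·(L − e)/(120·L) = a(1 − f).
- Score ≥ 0.60 requires a ≥ 0.60/(1 − f).

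| f | required a | minutes per week |
|---|---|---|
| 0 | 60% | 72 |
| 25% | 80% | 96 |
| 37.5% | 96% | 115.2 |
| 40% | 100% | 120 |
| 50% | 120% | 144 |

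**Examples at exactly 120 minutes in every week after the start.**

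- 6-week phase (720 charged, 432 needed): start after 2 weeks, 480/720 = 66.7%; after 3 weeks, 360/720 = 50.0%.
- 12-week chemotherapy (1440 charged, 864 needed): after 4 weeks, 960/1440 = 66.7%; after 5 weeks, 840/1440 = 58.3%.
- 2-week chemoradiation (240 charged, 144 needed): after 1 week, 120/240 = 50.0%.

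**Where it can arise.** The shortest three-stage course is 6 + 2 + 4 = 12 weeks. Entry 9 weeks before surgery on that course is 3 weeks into a 6-week chemotherapy phase, so f = 50%. Entry at 6 weeks comes as chemotherapy ends; if the patient is still counted there, the score is 0/720. Recovery lasts at most 6 weeks and entry needs at least 6, so on the planned timetable recovery is not shortened.

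**Effect on a phase result, under assumption.** Let t be the share of patients who would be adherent on exposed time and q the share who start with more than 40% of the phase gone, all scored non-adherent. The expected observed rate is t(1 − q). The chance of meeting the 60% rule is the binomial probability of at least 24/40 or 27/45.

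| t | q | expected rate | chance, n = 40 | chance, n = 45 |
|---|---|---|---|---|
| 70% | 0 | 70% | 0.937 | 0.945 |
| 70% | 10% | 63% | 0.714 | 0.719 |
| 70% | 20% | 56% | 0.365 | 0.350 |
| 70% | 30% | 49% | 0.109 | 0.092 |
| 60% | 0 | 60% | 0.568 | 0.564 |
| 60% | 10% | 54% | 0.275 | 0.256 |
| 60% | 20% | 48% | 0.087 | 0.072 |
| 60% | 30% | 42% | 0.017 | 0.011 |

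**The case against.** The best defence is that the design presumes entry at the start of therapy. Being scheduled for therapy most naturally means that it has not begun. The Background places prehabilitation before acute treatment, Exercise Intervention has exercise running through the whole course, VII. Statistics counts all 35 three-stage patients in every phase, and Study Measures plans accelerometer monitoring in each phase. This stands as evidence of intent. It is not a requirement, and the formula has no safeguard if practice departs from it.

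Also in the plan's favour:

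- VII. Statistics speaks of weekly prescriptions, and a patient not yet enrolled has none. But the explicit formula uses total phase duration, and a later analysis plan that followed it would inherit the problem.
- Short delays from clearance or fitness testing do limited harm in long phases. One week lost raises the cut-off to 60%/(11/12) = 65.5% in a 12-week phase and 60%/(5/6) = 72% in a 6-week phase. Only in very short phases does a week decide the outcome.
- Minutes above target can offset a late start.
- For a programme whose feasibility includes getting started, a whole-phase denominator is a defensible conservative measure. That is a reason to report it alongside, not to let it alone define adherence.

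Two stronger readings are tempting and unsupported. A reader might infer that the 6-week criterion is a leftover from the first design, in which "we would assess the exercise intervention in a 6-week period regardless of the treatment phase". The protocol does not link the two, and 6 weeks is also the shortest complete course (2 + 4, chemoradiation then recovery). A reader might also infer that the lower chemotherapy compliance already reported is an artefact of this denominator. That remark comes from the first 20 patients under the old 6-week design, so nothing ties it to the present formula.

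**Conclusion.** The point holds in a conditional form. As written, the formula gives a wrong score to any patient who starts exercise after a phase has begun, and the inclusion criteria do not exclude such patients. The rise in the cut-off to 60%/(1 − f), and the certain failure above f = 40% for a patient at exactly 120 minutes per week, follow from the protocol's own numbers.

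The size of any bias in the phase results does not follow from them, because the number of late starters is unknown. It is nil if all patients are taught the exercises before therapy. With 10% late starters and 70% truly adherent, the chance of meeting the rule with n = 40 falls from 0.937 to 0.714, assuming that all of them are past 40% of the phase and all are scored non-adherent. It would go too far to say that adherence is biased downward, or that the protocol sets up a late-entry window; the documents show neither. This is a worthwhile correction to the primary-endpoint definition, not a proven flaw in the results.

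**What to change.** In VII. Statistics, define prescribed minutes for a phase as 120 × weeks from the later of phase start and date of exercise instruction to phase end. Count a patient in a phase only if instruction preceded the end of that phase. Report the whole-phase denominator as a sensitivity analysis.

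Patients taught before the phase starts keep the same score, and a late starter who does 120 minutes every remaining week scores 100%. The weekly prescription and the eligibility criteria need no change. I would not add a fixed minimum exposure: even two weeks is the whole of the shortest chemoradiation phase, so one day's delay would remove the patient.

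The cost is one extra date per patient. A few patients may leave a phase's denominator, so the planned 40 and 45 could become slightly smaller and the intervals slightly wider.

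### The primary endpoint's adherence rule is not consistent between Adherence/compliance and VII. Statistics, and the pooled-minutes calculation can class a patient who did no strengthening as adherent

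*Protocol*

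**What the plan says.** All references are to the prehabilitation protocol (2014-0702).

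VII. Statistics describes adherence in three steps.

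- It opens with a total-time definition: at least 60% of the planned exercise, judged by time spent relative to the length of the phase.
- It restates this for the feasibility decision. A phase is feasible if at least 60% of participants "complete at least 60% of the weekly prescriptions for 60 minutes of walking and 60 minutes of strengthening" exercises.
- It sets out the calculation. "The target weekly total exercise hour will be 120 minutes (including 60 minutes of walking and 60 minutes of strengthening exercises"), and this is multiplied up to the length of the phase. Then, "based on the recorded total hours of exercise intervention for that patient, we can calculate the % of completion for that patient". The cut is single: "If the % is at least 60% for a phase, we would define that patient as" adherent for that phase.

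The Adherence/compliance section of VI. Study Plan gives a different basis: "Adherence to the program will be based on completion of a variety of strengthening exercises (eight or more per session) and the total time spent" on the two components. It then describes full adherence by component: "A participant who is able to complete 60 minutes of walking and 60 minutes of resistance exercise per week during each phase" of neoadjuvant therapy is classed as 100% adherent in that phase.

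The walking prescription is a range: "The walking program will consist of walking briskly for a duration of 20 - 30 minutes per day", on three or more occasions a week. Strengthening is prescribed as 30 minutes, two or more times a week (A. Resistance/strengthening).

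**The concern.** Feasibility, based on adherence to the exercise intervention, is the only primary endpoint. Adherence (yes/no) is also the outcome of the exploratory logistic models. The rule therefore needs to give one answer from one set of logs, and to reflect a program with two components.

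The calculation in VII. Statistics lets minutes of one component stand in for minutes of the other. The denominator credits walking with 60 minutes a week, but the walking prescription already reaches 90 minutes at three sessions and sets no upper frequency. Walking beyond 60 minutes can therefore fill the place of strengthening that was not done. The exercise-count element in Adherence/compliance would expose this, but the calculation does not use it.

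At stake is what a positive result means. The revised design is meant to identify the best phase or phases for delivering the exercise intervention. A phase could look favorable because patients walked more, while the resistance component was poorly taken up.

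**Working it through.** **Inputs**

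- Weekly target: 120 minutes, made up of 60 walking and 60 strengthening (VII. Statistics).
- Patient cut: 60% of the phase total (VII. Statistics).
- Feasibility cut: 60% of patients in the phase (VII. Statistics).
- Walking prescription: 20 to 30 minutes, three or more times a week, so 3 × 20 = 60 to 3 × 30 = 90 minutes at three sessions (B. Walking program).
- Strengthening prescription: 30 minutes, two or more times a week (A. Resistance/strengthening).
- Planned numbers per phase: 40, 45 and 50 (VII. Statistics).

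**The plan's own figures.** Exact (Clopper-Pearson) 95% intervals at 60% adherence:

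- 24/40: 43.3% to 75.1%
- 27/45: 44.3% to 74.3%
- 30/50: 45.2% to 73.6%

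These agree with the stated (43%, 75%), (44%, 74%) and (45%, 74%). The precision statement is correct.

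**The two rules**

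- Pooled: (walking + strengthening) / 120 ≥ 0.60, so the cut is 0.60 × 120 = 72 minutes a week on average over the phase.
- Component-wise: walking / 60 ≥ 0.60 and strengthening / 60 ≥ 0.60, so the cut is 0.60 × 60 = 36 minutes a week of each, on average over the phase.

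**Applied to average weekly minutes**

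| Walking | Strengthening | Pooled completion | Pooled rule | Component-wise rule |
|---|---|---|---|---|
| 60 (3 × 20) | 0 | 60/120 = 50% | not adherent | not adherent |
| 72 (3 × 24) | 0 | 72/120 = 60% | adherent | not adherent |
| 80 (4 × 20) | 0 | 80/120 = 66.7% | adherent | not adherent |
| 90 (3 × 30) | 0 | 90/120 = 75% | adherent | not adherent |
| 120 (4 × 30) | 0 | 120/120 = 100% | adherent | not adherent |
| 0 | 90 (3 × 30) | 90/120 = 75% | adherent | not adherent |
| 60 | 12 | 72/120 = 60% | adherent | not adherent (12/60 = 20%) |
| 55 | 30 | 85/120 = 70.8% | adherent | not adherent (30/60 = 50%) |
| 36 | 36 | 72/120 = 60% | adherent | adherent |

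Every walking-only row uses sessions that the walking prescription allows. The 120 + 0 row scores 100% under the pooled calculation, whereas Adherence/compliance describes 100% adherence as 60 minutes of each component.

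**Direction of change.** A patient who meets both component cuts averages at least 36 + 36 = 72 minutes a week and so also meets the pooled cut. The reverse does not hold. Moving to the component-wise rule can therefore leave the observed rate the same or lower it, but cannot raise it.

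**Sensitivity of the decision.** At the planning rate of 60%, one reclassified patient is enough to change the result: 24/40 = 60% is feasible and 23/40 = 57.5% is not.

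**The case against.** The strongest reply is that VII. Statistics leaves little doubt about which calculation will be run. Two of its three statements are plainly pooled. The middle one is introduced as a restatement and can be read as the same 120-minute total, since it never says 60% of each. Adherence/compliance also refers to total time, and its description of full adherence is compatible with a pooled 60% cut for partial adherence. Much of this stands. The sentence in VII. Statistics permits a component reading but does not compel it. If it is read as pooled, though, the walking-only result remains, and the exercise-count element is still present in one section and absent from the other.

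A reader might infer more than the documents support, in three ways.

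- *That feasibility would be declared with no strengthening done.* The rule permits this only if at least 60% of a phase's patients (24 of 40, for example) average 72 minutes or more of walking with no strengthening. That is an extreme case. Nothing in the protocol predicts it, and the 60% cut does exclude a patient who walks exactly 60 minutes and does nothing else.
- *That scoring over the whole phase is a mistake because active weeks can offset idle ones.* In a 12-week phase, 5 weeks at 180 minutes and 7 at zero give 900/1,440 = 62.5%. But VII. Statistics deliberately measures time against the length of the phase, so this is a stated choice.
- *That minutes must be capped each week.* No section mentions a cap, and the inconsistency can be resolved without one.

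It is also fair to say that a shortfall in strengthening would not be hidden from the investigators. Strengthening time and walking time are logged separately, patients are telephoned every two weeks, and tolerance for specific exercises is summarized. These measures do not enter the primary endpoint.

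Finally, a component-wise rule is stricter. The patient at 55 + 30 minutes completes 70.8% of planned time and would fail it, which departs from the opening total-time definition. This is a reason to make the choice explicitly.

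**Conclusion.** The point holds in a limited form. The protocol does not give one consistent definition of adherence for its sole primary endpoint. The calculation it sets out has no component minimum, so a patient averaging 72 to 90 minutes of walking a week over three prescribed sessions, with no strengthening, scores 60% to 75% and counts as adherent. This does not fit the Adherence/compliance section, nor the component reading of the weekly-prescriptions sentence.

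The conclusion assumes that recorded minutes count in full, because no limit is stated. How many patients would be classified differently cannot be estimated from the protocol, so the effect on the feasibility result is unknown. Its direction is known: the pooled rule gives a rate at least as high as the component-wise rule. The sample sizes and planned confidence intervals are unaffected. This should be fixed, but it does not invalidate the pilot.

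**What to change.** Reconcile Adherence/compliance and VII. Statistics into one primary definition that settles two questions:

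1. Does the 60% apply to the pooled total, or to walking and strengthening separately over the phase?
2. Does the number of strengthening exercises per session count toward adherence, or is it only described?

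Applying 60% to each component over the phase fits the two-component program. The pooled total-time rule would then be reported as a sensitivity analysis. If the pooled rule is kept as primary, report adherence by component beside it and word the feasibility conclusion as one about total exercise time. No weekly cap is needed, and the exercise prescription is not affected.

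The cost is a wording change and a few lines of code on minutes already logged separately for the two components. The downside is that the observed adherence rate may fall under the component-wise rule, so a phase near 60% could be judged not feasible.
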